### Measures

To evaluate the multidimensional study aims, a series of outcome measures will be used before (baseline) and 1 and 2 years after the intervention at the following levels: (1) child, (2) caregiver and (3) community (see figure 3). The outcome measures were selected and modified by the international team of experts, a team from Malamulele Onward in South Africa, and a local team of therapists and social workers living in the region. We selected gold standard outcome measures when possible, but since the context in LMICs differs from HICs, some tools needed to be modified, and others were selected among tools previously used in other low-resource settings (see online supplemental file 1).

**Figure 3 F3:**
[figure not shown]
Akwenda CP programme overview with the five components, three levels, three goals and all outcome measures. See online supplemental file 1 for detailed background and design of the programme. CP, cerebral palsy; GAS, Goal Attainment Scale; GMFM-66, Gross Motor Function Measure; PEDI-UG, Uganda version of Pediatric Evaluation of Disability Inventory; PedsQL, Pediatric Quality of Life Inventory; PMP, Picture my Participation; ZCCS, Zimbabwe Caregiver Challenges Scale.

#### Background characteristics

Background data will be collected on all children before allocation to groups. This includes sociodemographic information and medical history: Gross Motor Function Classification System, Manual Ability Classification System, Communication Function Classification System; clinical and nutritional examinations including anthropometric data; information on school attendance, care seeking, and need for and current usage of TAD.

#### Child-related outcome measures

##### Gross Motor Function Measure-66

The Gross Motor Function Measure-66 will be used as the primary child-related outcome. It is a clinical tool regarded as the gold standard when evaluating change in gross motor function in children with CP.^47^

##### Uganda version of Pediatric Evaluation of Disability Inventory

This is a parent-reported measure of the child’s independence in self-care, mobility and social function widely used in both research and clinical practice. The Pediatric Evaluation of Disability Inventory was developed in North America and has recently been culturally adapted and translated to the Ugandan context.^48 49^

##### Picture my Participation

Picture my Participation is an instrument designed to assess the participation of children, particularly in LMICs.^50^ It measures attendance and involvement in 20 activities.

##### Goal Attainment Scale

Goal Attainment Scale (GAS) is an objective method of quantifying goal attainment that has been widely applied to children with CP.^41^ Goals are scored on a 5-point Likert-type scale from no change at all to attainment of goal at much more than the expected level. This measure will only be used in the intervention group.

##### Evaluation of TAD

A goal for the use of the assistive devices will be set for each child in the intervention group, and the GAS scale will be used to evaluate the use of assistive devices. User satisfaction will be evaluated at the end of the intervention using a questionnaire based on the Quebec User Evaluation of Satisfaction with Assistive Technology adapted to Uganda.^51^

#### Caregiver-related outcome measures

##### A Knowledge Questionnaire evaluating caregiver’s learning outcomes

A Knowledge Questionnaire evaluating caregiver’s learning outcomes from the caregiver-led workshops will be administered before and after the workshop. This questionnaire comprises 26 statements, with three possible responses: agree, disagree or not sure. It is based on the Knowledge Questionnaire developed to evaluate the MOC2CTP. It was modified during the piloting phase; two statements were removed because they were ambiguous and one statement was rewritten to provide greater clarity.

##### Caregivers’ skill and behaviours

Interaction, skills and behaviours of caregivers performing two everyday activities with their child: that is, dressing and undressing; and feeding in the child’s home will be captured in two videos, each 4 min long. The assessment of the video clips has been developed and used by Malamulele Onward and further adapted by the research team for this study. Five observable behaviours will be scored using a 4-point Likert scale, with 0 being ‘none of the time’ and 3 being ‘90% or more of the time’.

##### Caregivers’ quality of life

Caregiver quality of life will be assessed using the 36-item PedsQL Family Impact Module, which is a validated and reliable measure.^52^ This was successfully used in a similar study in Ghana,^21^ and has been translated into Luganda, the local language.

##### Caregivers’ stress

Caregiver stress will be assessed using the Zimbabwe Caregiver Challenges Scale.^53^ This tool was recently developed for caregivers of children with lifelong disabilities living in low-resource African settings.

#### Community-related outcome measures

##### Communication and Advocacy Survey Questionnaire

This tool is based on the Christian Blind Mission Inclusive Development Tool Kit^54^ and comprises 44 items measuring the knowledge, attitudes and practices of community members. The tool, available in both English and Lusoga, has been developed by the research team and pretested on community members in Uganda.

### Data collection, management and analysis

#### Organisation and management

The Akwenda CP programme is a study within the CURIE research consortium, a collaboration between the Makerere University College of Health Sciences, Kampala, Uganda and Karolinska Institutet, Stockholm, Sweden, and clinical researchers from South Africa and the USA. The project will be guided by a steering group ensuring the conduct and coordination of the study. There will be a local Site Steering Committee consisting of the principal investigator (PI) ([name]), an administrative project manager, a PhD student and a parent carer. The project manager will be coordinating the study on site and report to the PI.

#### Data collection and monitoring

Two therapists not involved in the intervention will administer the baseline and outcome assessments. They have preknowledge of the project from participating in the development of the intervention, and will be trained over a period of 4 weeks in the assessments. The PhD student, also a therapist, will assist in the assessments and be responsible for data collection, storage and analysis. A data manager will supervise the overall organisation, storage and security of the data and ensure information is recorded accurately.

#### Data management and analysis

Data will be collected in Open Data Kit using tablets, and electronic data will be managed through a secure database. The use of electronic data collection with built-in quality control will minimise missing or inaccurately entered data. The researchers will supervise data collection and monitor the database in real time to address any quality issues that might be arising. Data will be analysed using Stata version 14.2. Standard analysis methods for a randomised controlled trial, including general linear mixed models, will be used to make comparisons between the intervention group and the waitlist group on an intention-to-treat basis. Effect estimate will be presented as a mean difference and 95% CI. Secondary outcome analyses will use similar methods to compare all other outcomes between groups immediately post-intervention and again 1 year later. The GAS goal attainment scores for the intervention group will be analysed with paired t-tests on a within-group basis. A senior statistician will guide and assist with the analysis.

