**Methods:**

This quasi-randomised controlled clinical study will recruit children and youth with CP aged 2–23 years in a rural area of Uganda. Children will be allocated to one of two groups with at least 44 children in each group. Groups will be matched for age, sex and motor impairment. The intervention arm will receive a comprehensive, multidimensional programme over a period of 11 months comprising (1) caregiver-led training workshops, (2) therapist-led practical group sessions, (3) provision of technical assistive devices, (4) goal-directed training and (5) community communication and advocacy. The other group will receive usual care. The outcome of the intervention will be assessed before and after the intervention and will be measured at three levels: (1) child, (2) caregiver and (3) community. Standard analysis methods for randomised controlled trial will be used to compare groups. Retention of effects will be examined at 12-month follow-up.

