## Methods

### Study design

The project is designed as a quasi-randomised controlled clinical study conducted according to the Standard Protocol Items: Recommendations for Interventional Trials guidelines (see figure 1). Children with confirmed diagnoses of CP will be assigned to either a study group or control group, based on geographical regions. The study group will receive the Akwenda CP programme during the first year, while the control group will be on a waitlist and receive usual care. The control group will receive the intervention after 1 year. Children and caregivers of the first intervention group will be encouraged to continue with the parent-led workshops and to implement new caregiving skills and behaviours during the second year. Both groups will be assessed prior to the start of the intervention, after 1 year and after 2 years.

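### The between-group comparison of secondary outcomes at 2 years contrasts early with delayed start, so it cannot measure retention or programme versus usual care

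*Protocol article*

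**What the plan says.** The Study design section describes a waitlist trial. In year 1 the study group receives the programme, "while the control group will be on a waitlist and receive usual care". Then: "The control group will receive the intervention after 1 year". The visits are common to both arms: "Both groups will be assessed prior to the start of the intervention, after 1 year and after 2 years". In year 2 the first group's children and caregivers "will be encouraged to continue with the parent-led workshops".

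The abstract describes a "comprehensive, multidimensional programme over a period of 11 months" and adds: "Retention of effects will be examined at 12-month follow-up". It names no method for that examination.

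The Data management and analysis section says that standard trial methods, including mixed models, "will be used to make comparisons between the intervention group and the waitlist group on an intention-to-treat basis". It continues: "Secondary outcome analyses will use similar methods to compare all other outcomes between groups immediately post-intervention and again 1 year later". The only within-group analysis named is the paired t-test on Goal Attainment Scale scores in the intervention group.

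**The concern.** Read against the Study design section, the second comparison falls at the 2-year visit. By then the waitlist group has been offered the same programme that the first group had in year 1. The analysis section nevertheless plans a comparison of the same kind as at year 1 and does not say that its meaning has changed.

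The stake is interpretation. The abstract promises a result on retention, and this contrast is the only between-group analysis at that visit in the text shown. If it were used for that purpose, a programme that worked and lasted in both groups could give a difference near zero. A programme that worked but partly faded could give a difference in favour of the waitlist group.

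**Working it through.** **Step 1. Exposure at each visit** (Study design section; programme length from the abstract).

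| Visit | First group | Waitlist group |
|---|---|---|
| Baseline | not yet treated | not yet treated |
| Year 1 | 11-month programme just offered | usual care only |
| Year 2 | about a year past the programme, encouraged to continue workshops | 11-month programme just offered |

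An 11-month programme fits between the year-1 and year-2 visits. Only the year-1 row sets treated against untreated. Aligning each group to the end of its own programme does not help, because the stated schedule has no visit one year after the waitlist group's programme.

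**Step 2. What the year-2 contrast estimates.** Let D be the programme effect at year 1, r the share of D that the first group still has at year 2, and g the share of D that the waitlist group gains in year 2. With the same background trend in both groups:

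expected year-2 difference = D × (r − g)

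Retention is r. Programme versus usual care would need g = 0. The contrast gives only r − g. Full retention with full waitlist gain (1, 1), half with half (0.5, 0.5) and none with none (0, 0) all give zero, whatever D is. This step uses no sample-size input, and a larger trial would not change it.

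**Step 3. Inputs for an illustration** (Sample size section): difference 12.5 points, SD 18.6, 44 per group with 10% loss, so 44 × 0.9 = 39.6 analysed per group. Two-sided 5% is assumed, because the section does not state sidedness. These inputs are for PedsQL, a primary outcome. The document gives no SD for a secondary outcome.

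**Step 4. The plan's own figure.** SE = 18.6 × √(2/39.6) = 4.18. Detectable difference at 80% power = (1.960 + 0.842) × 4.18 = 11.7 (11.9 with the t distribution). The stated 12.5 is not reproduced exactly, but it errs on the cautious side: power at 12.5 is about 85%. Nothing below depends on this gap.

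**Step 5. Expected year-2 differences with D = 12.5.** The chance of significance in the direction of the expected difference is Φ(|d|/SE − 1.96). For d = 6.25: 6.25/4.18 = 1.495, and Φ(1.495 − 1.96) = Φ(−0.465) = 0.32. The values of r and g are assumptions, shown as a range.

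| Kept by first group (r) | Gained by waitlist group (g) | Expected difference | Chance of significance in that direction |
|---|---|---|---|
| 100% | 25% | 9.4 | 61% |
| 100% | 50% | 6.3 | 32% |
| 100% | 75% | 3.1 | 11% |
| 100% | 100% | 0 | 2.5% each way |
| 75% | 100% | -3.1 | 11% |
| 50% | 100% | -6.25 | 32% |
| 0% | 100% | -12.5 | 85% |

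The probabilities treat children as independent. Allocation is by village, into two geographic groups, with one coin flip (Randomisation and blinding section), so they are rough. The expected differences do not depend on that assumption.

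**The case against.** The strongest defence is that early versus delayed start is a legitimate contrast in a waitlist trial, and that the article never calls its year-2 comparison a retention test. A full protocol or analysis plan may define retention separately. Part of this stands: the contrast itself is not invalid, and a wrong report is not certain. But the article does more than leave the matter open. It commits to repeating the group comparison at year 2 by methods like those used at year 1, promises a retention result at the same follow-up, and gives no other meaning to the contrast.

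A reader might infer three stronger points that the document does not support.

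- *That kept gains must show up as a lost effect.* The difference reaches zero under full retention only if the waitlist group gains as much as the first group did. A smaller gain shrinks the difference in proportion.
- *That the year-1 result is diluted as well.* This would need a mixed model with one group effect across both follow-ups. The article does not state such a model, and naming two time points suggests one comparison per visit.
- *That the primary outcomes are caught by the sentence.* It covers the other outcomes. No year-2 group comparison of GMFM-66 or PedsQL is stated, so the PedsQL figures above only illustrate the mechanism.

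**Conclusion.** The point holds as a fault in a stated analysis. The year-2 comparison of secondary outcomes has no usual-care group, and its expectation is the effect kept minus the effect gained, so it cannot answer the retention question or the efficacy question. That conclusion rests only on the visit schedule, the programme length and the crossover of the waitlist group, assuming the waitlist group takes up the programme and benefits to some degree.

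The size depends on two unknown shares. On the illustrative PedsQL scale, full retention is compatible with expected differences from 9.4 down to 0 as the waitlist gain rises from 25% to 100%. Half retention with a full waitlist gain gives -6.25. The year-1 comparison is untouched by this flaw, which says nothing about its other limits, such as allocation by two regions.

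**What to change.** In the Data management and analysis section:

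1. State that the year-1 visit, before the waitlist group starts, is the only comparison of programme with usual care, for all outcomes. Including GMFM-66 and PedsQL is prudent, because the outcome measures are planned at both follow-ups.
2. Assess retention within the first group, as mean change from year 1 to year 2 and from baseline to year 2 with 95% CIs. Label it uncontrolled, and note that this group is encouraged to continue workshops in year 2.
3. Label any year-2 between-group contrast *early versus delayed start*, and draw no retention or efficacy conclusion from it.

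Optionally, report the waitlist group's change from year 1 to year 2 as supportive before-after evidence.

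The cost is wording and a few model contrasts, with no new data, visits or participants. The downside is that retention becomes an uncontrolled estimate, since the control group has crossed over by the 2-year visit.

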### Patient and public involvement

The Akwenda CP programme and the study design have been developed in collaboration with caregivers, community leaders and local health professionals. All of these stakeholders were invited to a dissemination event in January 2019 where the results from the first screening study from 2015 were reported. At the same time, plans for a 4-year follow-up study and this intervention study were presented and discussed. Local therapists and social workers from the region, together with four caregivers, have thereafter participated in the development and adaptation of the intervention programme (see online supplemental file 1), and in designing and planning the study. The parent-led workshop series, a core part of the intervention programme, was developed and refined by a team of therapists and the parents of children with CP in South Africa.

### Ethics and dissemination

#### Ethics

The research project has been reviewed by the Higher Degrees Research and Ethics Committee, School of Public Health, College of Health Sciences, Makerere University (Ref: 727) and approved by the Uganda National Council for Science and Technology (SS 5173). Written informed consent for study participation will be obtained from the mother or legal guardian, and, if possible, assent will be obtained from children above 8 years. The electronic data will be managed through a secure database. Participants’ identities will not be revealed in any publications or reports emanating from this study. Video file names will be de-identified. A study protocol including all items of the WHO Trial Registration Data Set has been completed and the study has been registered in accordance with WHO and ICMJE standards. Any amendment of the study protocol requires approval from the Research and Ethics Committee.

#### Safety

As the study is not a drug trial, there is no Data Safety Monitoring Committee. A COVID-19 risk management protocol has been developed and approved by the Higher Degrees Research and Ethics Committee, School of Public Health, College of Health Sciences, Makerere University and will be strictly adhered to. Any adverse events associated with the study will be screened weekly by the treating therapists, and reported to the PI, and referred to the Ethics Committee if considered serious. Any decision to describe interim results or terminate the trial will be made by the investigators with oversight from the Ethics Committee.

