#### Therapist-led practical group sessions and workshops

Trained paediatric occupational and physiotherapists will run monthly practical sessions for groups of caregivers, based on the material covered in the caregiver-led workshops. The emphasis of the practical sessions is on active caregiver participation and includes training caregivers to facilitate their children’s active participation and engagement. The sessions will be structured such that the therapist will be able to give each child individual attention during group activities. The parent facilitators will assist the therapists during these practical sessions. The therapists will in addition run four workshops including (1) technical assistive devices (TADs); (2) goal-based training; (3) nutrition and (4) epilepsy (see figure 2 and online supplemental table 2). To ensure consistency and quality, a therapist manual was developed for the intervention.

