### Standard care arm

Standard or usual care refers to that available for children with CP in the study area. Currently, children have access to primary healthcare and the local hospital. Support and services are rare in this rural setting with no specialised services at the local public hospitals or health centres. There are some private actors and non-governmental organisations working in the surrounding area, which may provide occasional sessions of physiotherapy or occupational therapy, and unpredictable donations of TADs such as wheelchairs or crutches.^4^ Caregivers in the usual care group will be asked to keep a monthly care diary during the waiting period.

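### In year 1 the stated adverse-event route reaches only the treated arm and the care diary only the usual-care arm, so neither harms nor outside care has a matching record in both arms

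*Protocol article*

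**What the plan says.** **Harms.** The protocol article's Safety section states: "Any adverse events associated with the study will be screened weekly by the treating therapists, and reported to the PI". Events considered serious then go to the Ethics Committee. The same section says: "As the study is not a drug trial, there is no Data Safety Monitoring Committee". No other adverse-event procedure is described.

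**Who has a treating therapist.** Under Therapist-led practical group sessions and workshops, "Trained paediatric occupational and physiotherapists will run monthly practical sessions for groups of caregivers"; therapists also assess devices and support goal setting in the intervention arm. For year 1 of the other arm, Study design says "while the control group will be on a waitlist and receive usual care". Of that usual care, Standard care arm says: "Support and services are rare in this rural setting with no specialised services at the local public hospitals or health centres".

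**Outside care.** Standard care arm mentions private and non-governmental providers in the surrounding area, "which may provide occasional sessions of physiotherapy or occupational therapy, and unpredictable donations of TADs such as wheelchairs or crutches". It then says: "Caregivers in the usual care group will be asked to keep a monthly care diary during the waiting period". For the whole sample, care seeking and device use appear only under Background characteristics: "Background data will be collected on all children before allocation to groups".

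**Allocation.** Randomisation and blinding describes neighbouring villages grouped into two geographic blocks, with a coin flip deciding which block starts first.

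**The concern.** Two kinds of information are collected by a route that exists in one arm only.

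Harms are picked up by staff who see the treated arm, and the wording limits screening to events linked to the study. Seizures, admissions, injuries and feeding problems can be expected in children with cerebral palsy whether or not they are in the programme. To judge whether the programme changes their frequency, the usual-care frequency must be known and events must be recorded before anyone judges their cause.

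Outside therapy and donated devices are presumably what the care diary captures, and it is kept only by usual-care caregivers. Such care could plausibly affect the primary child outcome, the GMFM-66. With one block per arm, uneven provider activity across the area falls wholly on one arm, and randomisation cannot average it out. At stake is whether the report can describe harms against a background, and whether it can say what care each arm received beyond the programme.

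**Working it through.** The article gives no event rate and no figure for outside care, so there is nothing of its own to reproduce. The check sets the sections side by side and then uses an illustration with assumed risks.

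**Step 1: routes in year 1, as stated.**

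| Information | Intervention arm | Waitlist arm |
|---|---|---|
| Adverse events between assessments | Screening by treating therapists (Safety) | None stated |
| Outside therapy, donated devices during follow-up | None stated | Monthly care diary (Standard care arm; content inferred from its name) |
| Care seeking, device use before allocation | Yes (Background characteristics) | Yes (same) |
| Assessments at baseline, 1 year, 2 years | Yes (Study design) | Yes (same) |

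The last two rows show what is symmetric. They do not fill the gaps. The background data precede allocation. The listed child, caregiver and community measures include none for harms or for care received from outside. The assessors who see both arms are given no adverse-event task in Randomisation and blinding or in Data collection and monitoring.

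**Step 2: effect on a harm comparison (illustration).** Inputs: 44 children per arm (Sample size); a true one-year risk p, equal in both arms, *assumed* to be 10%, 20% or 30%; detection *assumed* complete in the intervention arm and equal to s in the waitlist arm.

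Expected recorded events: 44p (intervention) and 44ps (waitlist). Apparent risk difference: p − ps = p(1 − s).

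| p | s | Intervention | Waitlist | Apparent difference |
|---|---|---|---|---|
| 10% | 0 | 4.4 | 0 | 10 points |
| 20% | 0 | 8.8 | 0 | 20 points |
| 30% | 0 | 13.2 | 0 | 30 points |
| 10% | 0.5 | 4.4 | 2.2 | 5 points |
| 20% | 0.5 | 8.8 | 4.4 | 10 points |
| 30% | 0.5 | 13.2 | 6.6 | 15 points |

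The true difference is zero in every row. Complete detection in the treated arm is the extreme case. If the restriction to study-related events lowers detection there, the apparent difference shrinks, but the treated arm's own rate is then understated.

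**Step 3: outside care.** With one block per arm, the observed difference in an outcome is the programme effect plus the effect of any difference in outside care between the two regions. The second term can be described only if outside care is recorded in both. A diary in one arm gives the level in one region and nothing to subtract it from.

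**The case against.** The strongest reply is that this is a condensed article. The therapist manual, the supplementary files and the full protocol are not shown and may hold a control-arm safety form or a wider diary. The Safety section does not say that waitlist events go unrecorded. This stands as a limit: that there is only one route is inferred from no other being described. It does not remove the point, because the article does more than stay silent. It assigns one procedure to staff whom only one arm has and the other to caregivers in only one arm.

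Second, the aims, measures and analysis sections promise no between-arm comparison of harms. That is correct, and it makes this a weakness of design and interpretation rather than an internal contradiction. The primary estimates are not altered by it.

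Third, the diary's content is not described. It might capture health events, which would narrow the harms gap, and logging the comparator is ordinary practice. Both remarks are fair. Neither supplies the missing record of outside care in the treated arm.

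Three stronger readings are tempting, but the documents do not support them:

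- *Deaths would be counted in one arm only.* Both arms are assessed at 1 and 2 years, the site is a demographic surveillance site, and the team has already established survival in this cohort (82 of 97). Deaths would probably surface in both arms. A mortality rate derived from those counts would measure expected deaths, not events missed.
- *Weekly screening contradicts monthly sessions.* The monthly sessions are one component, run for several groups. Therapists also run workshops, assess devices and support goal setting, and the timetable figure is not shown. No contradiction is demonstrated.
- *The diary biases the trial as extra attention.* Beside 11 months of programme contact in the other arm, a monthly diary is negligible.

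**Conclusion.** The point holds in a limited form. As written, year 1 has no stated route for non-fatal events in waitlisted children and no record of outside therapy or donated devices in the intervention arm to match the usual-care diary. Any statement on harms would rest on one arm, and a regional difference in outside care would be confounded with arm and invisible.

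The size cannot be fixed from the documents. Under the assumed risks of 10% to 30%, the spurious risk difference runs from 5 points (10% risk, half of waitlist events detected) to 30 points (30% risk, none detected).

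The conclusion rests on three assumptions: that the full protocol adds no further route, that the care diary logs care received, and that the treating therapists are those delivering the programme. It concerns year 1 only, since the waitlist arm enters the programme afterwards. It is an inexpensive improvement worth making, not a flaw in the primary analysis.

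**What to change.** Use the same monthly diary or contact form in both arms throughout year 1, with the same items and timing: outside therapy, devices received from other sources, and all adverse events (including admissions, seizures, injuries and feeding events) regardless of presumed relation to the study. Judge relatedness afterwards, as a separate field. Tabulate events and outside care by arm at year 1. If the full protocol already has a control-arm route, one sentence in the Safety section saying so would settle the harms half.

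The cost is an existing diary extended to about 44 more families, some added items for the 44 who already keep it, and the data entry. It has to be done prospectively, because analysis cannot recover events or care that were never recorded. Two-sided recording makes a regional difference in outside care visible, but it does not remove the confounding that comes from having one block per arm.
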